**Figure 1 F1:**
[figure not shown]
**Trial profile**.

### Interventions

Participants will be randomly allocated to one of two treatment arms: (i) ultrasound-guided injection of the plantar fascia with corticosteroid (experimental group), or (ii) ultrasound-guided injection of the plantar fascia with normal saline (control group). Prior to plantar fascia injection, participants in both groups will be given an ultrasound-guided posterior tibial nerve block with 2% lignocaine hydrochloride. All participants will be positioned prone on a treatment table with their knees extended. Corticosteroid injection will be performed with a 25 gauge (38 mm) needle and a 1 mL Luer-lock syringe containing 1 mL of 4 mg/mL dexamethasone sodium phosphate. Saline injection will be performed with a 25 gauge (38 mm) needle and a 1 mL Luer-lock syringe containing 1 mL normal saline (0.9% sodium chloride). For both injections, the needle will be inserted through the medial heel perpendicular to the long axis of the ultrasound transducer, and will be advanced under continuous guidance into the proximal plantar fascia [31]. Infiltration will occur near the calcaneal enthesis in the region of maximal fascia thickening. An aseptic technique will be used for all injections to minimise infection risk, including use of sterile gloves, sterile transducer covers and sterile transmission gel. Participants with bilateral plantar fasciitis will have both feet treated (with their allocated intervention) during a single appointment. Following treatment, participants will be advised to avoid all running and other high impact activities for at least 2 weeks.

Throughout the initial 8 weeks of enrolment, all participants will be required to complete a daily stretching program shown to decrease pain associated with plantar fasciitis [32]. The stretching technique requires participants to cross their affected leg over the contralateral knee in a seated position, then pull back on the toes until they feel a stretch in the arch of their foot. Participants will be instructed to repeat the stretch 10 times, with each stretch lasting for 10 seconds. All participants will be asked to complete the stretching program three times per day and to record their stretching frequency in a diary.

### Randomisation, treatment allocation and blinding

Treatment allocation will be performed according to a computer-generated randomised number sequence. Allocation will be concealed in a password protected computer file accessible by an investigator not involved in measuring outcomes ([name]). This investigator will also prepare the syringe prior to heel injection, thereby ensuring the investigator giving injections, measuring outcomes and analysing data ([name]) is blinded throughout the trial duration. As both treatment solutions (i.e. dexamethasone sodium phosphate and normal saline) appear in the syringe as clear liquids free from visible particulate matter, the syringe contents will not require masking. This protocol will also ensure that trial participants are blinded to their treatment allocation.

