**Methods:**

The trial will be conducted at the La Trobe University Podiatry Clinic and will recruit 80 community-dwelling participants. Diagnostic ultrasound will be used to diagnose plantar fasciitis and participants will be required to meet a range of selection criteria. Participants will be randomly allocated to one of two treatment arms: (i) ultrasound-guided injection of the plantar fascia with 1 mL of 4 mg/mL dexamethasone sodium phosphate (experimental group), or (ii) ultrasound-guided injection of the plantar fascia with 1 mL normal saline (control group). Blinding will be applied to participants and the investigator performing procedures, measuring outcomes and analysing data. Primary outcomes will be pain measured by the Foot Health Status Questionnaire and plantar fascia thickness measured by ultrasound at 4, 8 and 12 weeks. All data analyses will be conducted on an intention-to-treat basis.

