### Primary outcomes

Primary outcomes will be pain and plantar fascia thickness at 4, 8 and 12 weeks. Pain will be measured by the foot pain domain of the Foot Health Status Questionnaire (FHSQ), which has been shown to have a high degree of internal consistency (Cronbach's α = 0.88) and test-retest reliability (intra-class correlation coefficient = 0.86) [33]. Participants treated for bilateral plantar fasciitis will be asked to describe symptoms without specific reference to an individual foot (i.e. bilateral pain will be evaluated as one independent sample). Plantar fascia thickness will be measured by ultrasound at a standard location where the fascia crosses the anterior aspect of the inferior calcaneal border (Figure 2). This measurement technique has been shown to have good intra-rater reliability, with the 95% limits of agreement ranging from -0.7 mm to 0.5 mm [34]. Participants treated for bilateral plantar fasciitis will have thickness measurements taken for each individual foot. However, for bilateral cases, the mean change in plantar fascia thickness for the two feet will be calculated at each follow-up in order to evaluate data as one independent sample. Plantar fascia measurements and ultrasound guided injections will be performed with a variable frequency (5-10 MHz) linear array transducer (Acuson Aspen, Siemens Medical Solutions, Pennsylvania, USA).

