### Secondary outcomes

Secondary outcomes will be function, use of oral analgesic medication, and 'first-step' pain at 4, 8 and 12 weeks. Function will be measured by the foot function domain of the FHSQ, which has been shown to have a high degree of internal consistency (Cronbach's α = 0.85) and test-retest reliability (intra-class correlation coefficient = 0.92) [33]. Participants treated for bilateral plantar fasciitis will be asked to describe foot function without specific reference to an individual foot (i.e. bilateral function will be evaluated as one independent sample). Use of oral analgesic medication (including paracetamol, aspirin, opioids and non-steroidal anti-inflammatory drugs) will be recorded at each visit. 'First-step' pain, experienced when initially rising from bed in the morning, will be measured on a 100 mm visual analogue scale. Participants treated for bilateral plantar fasciitis will be asked to indicate the magnitude of symptoms without specific reference to an individual foot (i.e. bilateral pain will be evaluated as one independent sample).

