### Plantar fascia thickening

Fusiform thickening of the plantar fascia is a well established feature of plantar fasciitis. According to a meta-analysis of diagnostic imaging studies [28], people with plantar heel pain are over 100 times more likely to have an abnormally thickened (> 4.0 mm) plantar fascia compared with asymptomatic controls (odds ratio = 105.11, 95% confidence interval = 3.09 to 3577.28, *P *= 0.01). Abnormal thickening is also reported in the tendinopathy literature, and is thought to be the result of increased secretion of ground substance proteins (e.g. proteoglycans) and subsequent tissue oedema [14]. These changes are considered a response to acute tensile overload and may lead to reduced tissue stress by increasing cross-sectional area [14]. However, it is also noted that increased thickening is not a feature of normal tendon adaptation to chronic loading regimens [14,60], thereby suggesting that changes in tendon thickness are related to abnormal tissue substance.

In response to corticosteroid injection, plantar fascia thickness values have been shown to decrease significantly as early as two weeks [24] and one month [61] following treatment. One of these studies also reported a correlation between decreased plantar fascia thickness and pain relief (Pearson *r *= 0.61, *P *< 0.001) [61]. However, as neither of these studies made comparisons to a control group, it is possible that the findings were partly due to the condition's natural course. Nonetheless, a recent randomised trial reported a significant decrease in pain and plantar fascia thickness following injection with botulinum toxin, when compared to placebo injection [62]. This evidence suggests that plantar fascia thickness measurements can provide useful objective data, and may assist in identifying overall improvement in the condition.

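### One investigator, masked to allocation only, measures both symptoms and fascia thickness at the same visits, so a real effect on pain could leak into the thickness readings

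*Protocol article*

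**What the plan says.** The abstract's Methods paragraph states: "Blinding will be applied to participants and the investigator performing procedures, measuring outcomes and analysing data". The section on randomisation, treatment allocation and blinding explains how: a second investigator holds the allocation file and prepares the syringe, thereby "ensuring the investigator giving injections, measuring outcomes and analysing data" is kept blind for the whole trial. Of participants it adds: "This protocol will also ensure that trial participants are blinded to their treatment allocation". The masking described is masking to the arm.

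Under Primary outcomes: "Primary outcomes will be pain and plantar fascia thickness at 4, 8 and 12 weeks". Under Secondary outcomes: "Secondary outcomes will be function, use of oral analgesic medication, and 'first-step' pain at 4, 8 and 12 weeks". Analgesic use "will be recorded at each visit".

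On the precision of the ultrasound reading, Primary outcomes says: "This measurement technique has been shown to have good intra-rater reliability, with the 95% limits of agreement ranging from -0.7 mm to 0.5 mm". The Discussion section on plantar fascia thickening cites a correlation of 0.61 between thinning and pain relief in an earlier study and concludes: "This evidence suggests that plantar fascia thickness measurements can provide useful objective data".

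**The concern.** Masking to allocation stops the assessor from favouring an arm. It does not stop the assessor from favouring participants who have improved. The possible route runs from treatment to pain relief, from pain relief to what the assessor expects to see, and from there to where the calipers go. No step requires knowing the arm. If dexamethasone relieves pain, improved participants are commoner in that arm, and a tendency to read them as thinner becomes an error that differs by arm.

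The design leaves this route open because one person is responsible for measuring outcomes, and symptoms and thickness fall due at the same visits. The article also gives a reason to expect thickness to follow pain, namely the cited correlation. At stake is one of the two primary outcomes, the one the Discussion values for being objective. A thickness difference that partly echoes pain relief would overstate the drug's effect on the tissue.

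**Working it through.** **The plan's own figure.** Sample size section: difference 13, SD 20, alpha 0.05 (taken as two-sided), power 80%, loss 5%. n per group = 2 × (1.96 + 0.8416)² × 20² / 13² = 37.2, rounded up to 38. Allowing for loss, 38 / 0.95 = 40 per group. This reproduces the stated 40 and is not in dispute. The 38 analysed per arm is used below.

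**Repeat error of the reading.** The limits of agreement run from -0.7 to 0.5 mm, a span of 1.2 mm. SD of repeat differences = 1.2 / (2 × 1.96) = 0.31 mm. SD of a single reading = 0.31 / √2 = 0.22 mm. A shift of 0.1 to 0.3 mm would therefore not stand out from ordinary repeat error. This does not show that such a shift occurs.

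**Gap in improvement between arms.** The article gives no figure, so I bound it by the planning effect. For two normal distributions with SD 20 and means 13 apart, the proportions beyond a cut-off differ most when the cut-off lies midway: gap = 2 × Φ(13 / (2 × 20)) − 1 = 2 × Φ(0.325) − 1 = 2 × 0.6274 − 1 = 0.255, about 25 percentage points. This takes 20 as the SD of the score by which improvement is judged.

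**Spurious thickness difference.** Bias = shift in improved participants × gap. The shift of 0.1 to 0.3 mm is an assumption.
- Low: 0.1 × 0.255 = 0.025 mm
- High: 0.3 × 0.255 = 0.076 mm

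**False-positive rate for thickness with no true thickness effect.** SE = SD × √(2/38). Rate = 1 − Φ(1.96 − bias/SE) + Φ(−1.96 − bias/SE). The article gives no SD for thickness; 0.6 mm is an assumption, and the other rows show how far it matters.

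| Residual SD (mm) | SE (mm) | Rate, bias 0.025 mm | Rate, bias 0.076 mm |
|---|---|---|---|
| 0.5 | 0.115 | 5.6% | 10.2% |
| 0.6 | 0.138 | 5.4% | 8.6% |
| 0.75 | 0.172 | 5.2% | 7.3% |
| 1.0 | 0.229 | 5.1% | 6.3% |

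**No pain effect.** The gap is then 0, the bias is 0, and the rate stays at 5%.

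**The case against.** The strongest reply is that the article describes masking to allocation correctly and nowhere calls it sufficient. The order of procedures at a visit and the handling of images are details that an article may leave to a full protocol, which is not shown. That stands: their absence is not an error. The point rests on the combined role and shared visits, which the article does fix.

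Second, a reader might infer that the investigator hears about the pain and then scans. The documents do not say so. The pain questionnaire and the visual analogue scale are participant ratings, and nothing states who administers them, in what order, or whether the answers are seen before scanning. That one person takes every outcome is itself read from the singular wording. The concern is therefore conditional.

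Third, a reader might add that sight of earlier thickness readings biases the comparison. By itself it does not differ by arm, and it could pull readings towards no change, so it is not part of this point.

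Fourth, larger error rates are tempting. A 40-point gap in improvement with a 0.3 mm shift gives 0.12 mm and about 14% at an SD of 0.6 mm. Under the same normal model, that gap needs a pain difference of about 21 points (2 × 20 × 0.524), well above the planned 13.

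Fifth, it might be said that the relation between pain and thickness will be inflated. The Data analysis section plans no such analysis, and the Discussion says only that thickness can be useful and may assist.

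Finally, limits of agreement measure repeat error, including probe placement, and do not show that expectation moves calipers. The measurement site is already standardised. Both are fair; they are why the shift is labelled an assumption.

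**Conclusion.** The point holds in a limited form. One investigator, masked to allocation only, is responsible for measuring outcomes, and thickness falls due at the same visits as the symptom outcomes. If that person knows the symptoms when measuring, a true effect on pain could produce or enlarge an apparent effect on thickness.

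The bias is possible, not demonstrated. It needs a true pain difference, so it affects neither the pain outcome nor the thickness error rate when treatment leaves pain unchanged. On the assumptions of a 0.1 to 0.3 mm shift, a gap of at most about 25 points, a residual SD of 0.6 mm and 38 per arm, the spurious difference is up to about 0.08 mm and the false-positive rate about 5% to 9%. Only the 13 points, the SD of 20 and the numbers per arm come from the article. Severity is low: a cheap safeguard for one primary outcome, not the correction of a wrong statement.

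**What to change.** In the sections on blinding and on primary outcomes, state that follow-up ultrasound images are stored and that the same investigator measures them from coded files in random order, with participant, visit and symptom scores hidden.

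As a minimum, state that at each follow-up visit the thickness measurement is taken and recorded before any symptom data are seen, and that the participant is not told the reading. This is weaker, because the investigator may remember symptoms from earlier visits.

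If either step is already in the full procedures, one sentence in the article settles the point. Sample size, treatment, visits and staffing do not change. The cost is a little time to export and code images. One limit remains: acquiring the image is still done by someone who may recall the participant's earlier symptoms, so coded reading closes most of the route but not all of it.

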### Primary outcomes

Primary outcomes will be pain and plantar fascia thickness at 4, 8 and 12 weeks. Pain will be measured by the foot pain domain of the Foot Health Status Questionnaire (FHSQ), which has been shown to have a high degree of internal consistency (Cronbach's α = 0.88) and test-retest reliability (intra-class correlation coefficient = 0.86) [33]. Participants treated for bilateral plantar fasciitis will be asked to describe symptoms without specific reference to an individual foot (i.e. bilateral pain will be evaluated as one independent sample). Plantar fascia thickness will be measured by ultrasound at a standard location where the fascia crosses the anterior aspect of the inferior calcaneal border (Figure 2). This measurement technique has been shown to have good intra-rater reliability, with the 95% limits of agreement ranging from -0.7 mm to 0.5 mm [34]. Participants treated for bilateral plantar fasciitis will have thickness measurements taken for each individual foot. However, for bilateral cases, the mean change in plantar fascia thickness for the two feet will be calculated at each follow-up in order to evaluate data as one independent sample. Plantar fascia measurements and ultrasound guided injections will be performed with a variable frequency (5-10 MHz) linear array transducer (Acuson Aspen, Siemens Medical Solutions, Pennsylvania, USA).

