### Sample size

Prospective sample size calculation indicates a sample of 40 participants per group (i.e. 80 total) would provide 80% power to detect a minimal important difference of 13 points [35] on the pain domain of the FHSQ (SD = 20, alpha = 0.05, 5% loss to follow-up). The extra precision provided by covariate analysis was conservatively ignored when performing this calculation.

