### Data analysis

Statistical analyses will be undertaken using SPSS software (version 14.0 or later, SPSS Corporation, Chicago, IL, USA). Continuous data will be explored for normality using standard tests to satisfy the assumptions of parametric statistics. All analyses will be conducted on an intention-to-treat basis and missing follow-up data will be replaced with baseline observations carried forward (BOCF) (i.e. baseline data will be carried forward in circumstances where follow-up observations are missing). In comparison to a last observation carried forward (LOCF) approach, BOCF has been shown to provide a more conservative estimate when analysing the treatment effect of pain-relief medication [36]. Continuous outcomes with a normal distribution will be analysed using a linear regression technique with baseline measurements adjusted for by the analysis of covariance model (ANCOVA) [37]. If data is found to be not normally distributed, transformation will be attempted. However, if data is still not normally distributed after transformation, non-parametric statistical tests will be used. Other data (nominal or ordinal) will be analysed using appropriate non-parametric statistical tests. Statistical significance for hypothesis tests will be set at the conventional level of 0.05.

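### Six unranked primary comparisons share one 0.05 threshold, while the 80% power refers to a single pain comparison at an unnamed visit

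*Protocol article*

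**What the plan says.** The Primary outcomes section of the protocol article reads: "Primary outcomes will be pain and plantar fascia thickness at 4, 8 and 12 weeks". The Methods part of the Abstract says the same. Neither place ranks pain against thickness or one visit against another. For participants treated in both feet, the mean change in thickness "will be calculated at each follow-up in order to evaluate data as one independent sample", so thickness is derived visit by visit.

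The Data analysis section plans a baseline-adjusted analysis of covariance for continuous outcomes and names no test that combines the visits. It then fixes one threshold: "Statistical significance for hypothesis tests will be set at the conventional level of 0.05".

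The Sample size section arrives at 80 people, 40 in each arm, and claims that this number "would provide 80% power to detect a minimal important difference of 13 points [35] on the pain domain of the FHSQ". The inputs it lists are a standard deviation of 20, a 0.05 alpha and 5% attrition. It names no visit and makes no power statement for thickness.

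**The concern.** Two outcomes at three visits make 2 x 3 = 6 primary comparisons. An error rate of 0.05 and a power of 80% are properties of one comparison. They carry over to the trial's conclusion only if the plan says which comparison decides, or how the six combine, and this document fixes the threshold without doing either.

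The Conclusion says the findings will be used for evidence-based recommendations on corticosteroid injection. With six comparisons of equal rank, a mixed picture is likely and has no agreed interpretation. For example, a thickness difference at one visit with no pain benefit could be reported as a positive primary outcome. So could a pain difference at one visit out of three. A ranking made after unblinding would not be credible.

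**Working it through.** **Inputs from the protocol article.** Six primary comparisons (Primary outcomes); 0.05 per test (Data analysis); difference 13, SD 20, alpha 0.05, power 80%, loss 5%, 40 per group (Sample size). Sidedness is not stated. Two-sided is assumed because it reproduces the stated number; a one-sided test would need 30 per group before loss.

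**Inputs assumed.** The document gives no correlations between visits. I take 0.5 to 0.9 between visits of one outcome, and 0.3 to 0.6 between pain and thickness at the same visit. For different outcomes at different visits I use the product of the two. The only related figure in the document is r = 0.61 between thickness decrease and pain relief, which the Discussion cites from a study without a control group. It serves here only as a guide to the upper value.

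**1. The plan's own figure.** n per group = 2 x (1.960 + 0.842)² x 20² / 13² = 37.2, so 38. Allowing for 5% loss, 38 / 0.95 = 40. The stated 40 per group is reproduced. At 38 evaluable per group the power is 80.9% (normal approximation) or 79.9% (t-test). The sample-size arithmetic is sound for one pain comparison.

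**2. If any one of six counts as success.** With independent tests, 1 - 0.95⁶ = 0.265. With correlated tests, I simulated six two-sided z-tests under no effect (1,000,000 multivariate normal draws) and counted how often at least one |z| exceeded 1.96:

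| Between-visit correlation | Cross-outcome correlation | At least one false positive |
|---|---|---|
| 0 | 0 | 26.5% (exact) |
| 0.5 | 0.3 | 23.0% |
| 0.7 | 0.3 | 20.1% |
| 0.8 | 0.6 | 16.8% |
| 0.9 | 0.6 | 14.3% |

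**3. Pain alone at three visits.** With independent tests, 1 - 0.95³ = 0.143. By simulation it is 12.6% at between-visit correlation 0.5 and 8.4% at 0.9. Dropping thickness therefore reduces the problem but does not remove it.

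**4. If all six must succeed.** Each test is given 80% power, so its expected z is 1.960 + 0.842 = 2.80. For thickness this is an assumption, since the plan gives no power for it. The share of draws with all six significant is 41% (correlations 0.5 and 0.3), 47% (0.7 and 0.3), 55% (0.8 and 0.6) and 60% (0.9 and 0.6).

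**5. Cost of a plain correction.** Bonferroni over six gives 0.05 / 6 = 0.0083 per test. At 38 evaluable per group, power for one pain comparison falls to 58% (t-test 55%). Restoring 80% would take about 62-64 enrolled per group. Naming one deciding comparison leaves 40 per group, alpha 0.05 and 80% power as they are.

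**The case against.** **An analysis plan may add a multiplicity rule.** None is shown, and a missing adjustment would not by itself be a fair criticism of a journal article. This stands as a limit on the point. However, the article itself names the six primary comparisons and itself sets 0.05. A later correction would change that threshold and, as the Bonferroni figures show, would undo the power statement.

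**The protocol never says that one significant result makes the trial positive.** That is correct. A reader might infer that the trial runs a false-positive risk of about a quarter. The document does not support this: the inflation depends on an any-one-wins rule it does not state, and 26.5% needs independent tests. Three of the six are the same questionnaire in the same people, and three are the same fascia measurement. Carrying baseline values forward to every missed visit adds further dependence. The lower range is the fair one, and it too rests on assumed correlations.

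**The power figure may cover more than one comparison.** A reader might infer that 80% power covers only one of the six. That is too strong. No visit is named, and with the same SD and difference the 80% would hold for pain at each visit taken singly. Only thickness has no power statement.

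**The deciding visit could seem obvious.** A reader might infer from the Background that steroid works at one month and not at three, so that week 4 must be primary. The Background says only that no significant difference was detected at three months. Many participants had been lost, and the authors could not draw longer-term conclusions. The stated aim covers 12 weeks. The documents do not settle which visit should decide.

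**Pain and thickness are different constructs.** The Discussion presents thickness as useful objective data. That is a reason to measure and report it, but it does not tell a reader what to conclude when the two outcomes disagree.

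**Conclusion.** The point holds in this form. The protocol gives six comparisons equal primary rank and a common 0.05 threshold, while its power calculation describes one pain comparison at an unspecified visit. Under either simple reading, one of the two stated design figures fails to describe the trial's conclusion:

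- **Any one of six suffices:** the false-positive chance is about 14-23%, not 5%. The independence bound is 26.5%. For pain alone it is about 8-14%, the top value being independence.
- **All six are required:** joint power is about 41-60%, not 80%, with 80% power for thickness assumed.

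Both ranges depend on assumed correlations of 0.5-0.9 between visits and 0.3-0.6 between outcomes, and on decision rules that the document leaves open. Stronger correlation would narrow the gap; at the strongest values tried, the any-one-of-six figure is still nearly three times the nominal 5%. The sample-size calculation itself is not in error.

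**What to change.** Before unblinding, amend the protocol and registry wording as follows:

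1. Name FHSQ pain, the outcome the trial is sized on, as the single deciding primary comparison at two-sided 0.05. Take it at one visit chosen by the sponsor, or as one test of pain across the three visits. Either resolves the error-rate problem; the choice should follow from the trial's 12-week aim.
2. State that the 80% power applies to that comparison. If one test across visits is chosen, check that the power statement still fits it.
3. Report the group difference with its 95% confidence interval against the 13-point minimal important difference.
4. Test the other pain visits and thickness in a pre-stated order, each at 0.05 only while the one before it is significant, or report them as secondary without confirmatory claims. If an order is used, consider where early thickness sits: placed behind late pain, it may never be formally tested.

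The cost is wording only, with no extra patients or data. The downside is that thickness and the remaining visits lose stand-alone confirmatory status.
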